## Abstract

**Background:**

Many substance use disorder (SUD) care pathways exist in health care systems. However, patients with SUD often report poor care experiences, particularly regarding timely follow-up, clinician and general satisfaction ratings, and care communication. As SUD care pathways involve transitions across clinicians and venues of care, adequate treatment requires coordination across clinicians and settings to ensure unmet needs are addressed, and appropriate SUD care is delivered. Surprisingly little is known about the real-world care pathways patients engage in once identified as having SUD.

**Objective:**

This study protocol describes research that will comprehensively characterize the pathways of care used by those who obtain care for SUD and compare the quality and outcomes associated with these care pathways. Specific aims are to (1) apply multistate models (MSM) to characterize the spectrum of care transitions among patients with SUD within a large integrated health system, (2) generate data-driven insights to improve care delivery for SUD using estimated MSMs, and (3) observe and explore patient and clinician experiences with care transitions across common care pathways using qualitative methods.

**Methods:**

Quantitative data sources will include electronic health care records, insurance claims, self-reported measures of substance use and SUD symptoms, and death data from an integrated health care system in Washington State. To identify care pathways, we will apply continuous time, multistate modeling methods to empirically observe the longitudinal course of SUD care transitions undertaken by patients over time; each “state” or occurrence of care will be characterized by the intervention received (eg, evaluation or assessment, behavioral treatment or counseling, and pharmacotherapy) and setting of care (eg, outpatient, intensive outpatient, or inpatient or residential). The estimated parameters from the fitted MSMs will be transformed or interpreted to characterize SUD care quality, such as wait times for SUD visits, and receiving an adequate psychotherapy dose. To compare outcomes associated with care pathways, we will examine terminal states, including death and loss to follow-up. Using a mixed methods design, we will sample and interview patients engaged in empirically derived pathways to understand their care experiences, observe and interview clinicians to elucidate health system factors that impact SUD care transitions, and integrate qualitative and quantitative findings using joint displays.

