Studies of SUD care improvements require innovative approaches that consider the dynamic, longitudinal nature of treatment required to address SUD, which has been characterized as a chronic health condition [20,21]. The National Academy of Medicine has encouraged the application of systems approaches to improving health care [22]. As an approach for handling multiple events and time-to-event data within patients, multistate approaches conceptualize health care events and outcomes as states and capture the full sequence of a patient’s care and timing of transitions between states during a care episode [23]. From a multistate modeling perspective, care pathways are defined as the longitudinal sequence of SUD visits that begin where patients were identified (eg, primary care or emergency department [ED]), transition between SUD care types (eg, evaluation and assessment, behavioral treatment and counseling, and pharmacotherapy) [24-26] and settings visited (eg, outpatient, intensive outpatient, or inpatient or residential settings) [27,28], and end in terminal events, such as ceasing SUD care or death. These models capture the dynamics of how patients move through the health system and the probabilities or “intensities” of transitions between states. As a result, multistate approaches have the potential to generate meaningful insights that health systems can use to better organize care delivery for SUD.

This paper presents the protocol for a retrospective cohort study that will apply a multistate approach to nearly 10 years of data from the Kaiser Permanente Washington (KPWA) electronic health record (EHR). This includes health care encounters and patient-reported SUD outcome data from tens of thousands of patients. We will link EHR data to health insurance claims and Washington State death data. This will support a comprehensive exploratory analysis of SUD care transitions that will inform strategies to improve access, continuity, and outcomes in SUD treatment. It also describes our plans to use qualitative research methods to complement the quantitative findings, providing a mixed-methods approach to generate data- and human-driven insights for improving SUD care.

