### States for the MSMs

States will capture 3 types of events related to SUD care: initial states, transient states, and terminal states. Defining states requires a balance of specificity to produce actionable information, and parsimony to allow for an estimable statistical model with accurate estimates and smaller SEs.

Initial states in the MSMs represent the clinical settings that triggered an incident event at the start of an SUD care episode, corresponding to the 5 subcohorts in Table 1.

There are 3 types of transient states. The first type is care states, which include different types of care provided in the health care system to treat the SUD, defined by combinations of setting and service type (Table 2). We opted to define 15 preliminary SUD care states based on a combination of 3 settings and 5 service types. The second type of transient state is temporary discontinuation of care. Entry into the temporary discontinuation care state is triggered using a clinically meaningful threshold for time elapsed between SUD treatment visits. The last transient state is SUD remission, which represents an improvement in the patients’ disease.

**Table 2. T2:** Transient states and terminal states are represented in the multistate models.

Category	States included	Description
Transient states	A total of 17 transient states include 15 care states derived from crossing 5 service types with 3 care settings; temporary discontinuation of SUD^a^ care; and remission of use disorder.	Care states Service types Evaluation and assessment Behavioral treatment and counseling Prevention, education, and case management Pharmacotherapy Other service Settings Outpatient Intensive outpatient Inpatient or residential Other transient states Discontinuation of SUD care A lack of SUD care over a specified period^b^ Remission of use disorder Low risk score on alcohol and substance use screen; clinically meaningful reduction on screening scores or <2 symptoms on *DSM-5*^c^ checklist; SUD remission diagnosis
Terminal states	4 states representing the end of a care episode	Death, derived from dates in health care enrollment records or Washington State death data Loss to follow-up, defined as at least 31 days without KPWA insurance coverages Ceased SUD care (no medication fills or services with a qualifying SUD diagnosis for more than 194 days Administrative censoring (in the middle of a care episode when data collection ends)

a SUD: substance use disorder.

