### Study Outcomes

This study has 2 types of outcome assessments: outcomes associated with terminal states, such as the percentage of patients or time that it takes to get to a terminal state, and outcomes associated with pathways, such as achievement of guideline-concordant care (Table 2, Multimedia Appendix 1). Terminal states are explicitly modeled as states in MSMs, whereas the probability of receiving guideline-concordant care is derived from estimated transition probabilities (see subsection Aim 2. Generate Data-Driven Insights to Improve Care Delivery Using Estimated MSMs under the Statistical Analysis section).

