**Figure 3. F3:**
[figure not shown]
Transition-free (or survival) probability by initial access state (hypothetical). This hypothetical survival plot displays how the probability of not reaching a given state can be graphed as a function of the initial state. In this example, the probability of not reaching behavioral treatment and counseling in an outpatient setting (not shown) is markedly higher when the incident substance use disorder event occurs in the emergency department setting, when compared to primary care or behavioral health settings. Potentially, this is suggestive of inefficiencies in referring people from emergency department settings to behavioral treatment and counseling in an outpatient setting.

What is the contribution of care states in achieving terminal states? We will calculate restricted mean survival times (RMSTs) [69] between a given SUD care state and each terminal state. An example of RMST quantities between select care states and a terminal state is presented in Table 5. The RMST captures the average terminal-event-free time, which in this study reflects time before reaching a terminal state, calculated as the area under the terminal-event-free curve over a prespecified time interval since the entry to the given care state. Figure 4 presents an example of terminal-event-free curve estimates using states from Figure 1. In this example, care types that produce lower RMSTs are those more likely to end in ceasing SUD care. Identifying these care types can inform targeted efforts, such as enhancing care coordination or improving staff levels in specific settings or for patients who receive certain treatment modalities to increase retention in SUD care.

**Table 5. T5:** Restricted mean survival times (RMST) from selected care types to ceasing care.

Substance use disorder (SUD) care state	Follow-up time (days)		
	30	60	90
Behavioral treatment and counseling, outpatient	μ₁,₄(30)^a^	μ₁,₄(60)	μ₁,₄(90)
Evaluation and assessment, intensive outpatient treatment	μ₂,₄(30)	μ₂,₄(60)	μ₂,₄(90)
Pharmacotherapy, outpatient	μ₃,₄(30)	μ₃,₄(60)	μ₃,₄(90)

a 𝜇_i_,_𝑗_(𝑡_𝑜_) is the restricted mean survival times from state i to state j over time interval 𝑡_𝑜_, where i=1 (behavioral health counseling, outpatient), 2 (evaluation and management, intensive outpatient treatment), and 3 (pharmacotherapy, outpatient); j=4 (ceasing substance use disorder care).

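### No planned outcome comparison names remission, and ceased care pools patients who left in remission with those who disengaged, so a short time to ceasing care can reflect recovery as well as poor retention

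*Protocol article*

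**What the plan says.** The Objective in the Abstract is to characterise SUD care pathways and compare their quality and outcomes. The Abstract's Methods paragraph bases the outcome comparison on terminal states: "To compare outcomes associated with care pathways, we will examine terminal states, including death and loss to follow-up". Study Outcomes gives two types. The first is "outcomes associated with terminal states, such as the percentage of patients or time that it takes to get to a terminal state". The second type, which is derived from the estimated transition probabilities, is "outcomes associated with pathways, such as achievement of guideline-concordant care".

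Table 2 (States for the MSMs) lists "4 states representing the end of a care episode": death, loss to follow-up through loss of coverage, ceased care, and administrative censoring. The third is defined as "Ceased SUD care (no medication fills or services with a qualifying SUD diagnosis for more than 194 days", with no reference to whether the patient had improved.

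The same section handles improvement separately: "The last transient state is SUD remission, which represents an improvement". Remission is built from screening scores, symptom checklists and remission diagnoses. The Introduction describes the source as including "patient-reported SUD outcome data from tens of thousands of patients".

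Under Aim 2, the contribution of care states is measured by RMST from a care state to each terminal state. The text explains: "In this example, care types that produce lower RMSTs are those more likely to end in ceasing SUD care". It adds that finding these care types can guide work on coordination or staffing to raise retention. Sequence probabilities run from an initial state to a terminal state. The subgroup comparison is of terminal states, for example at one year. Of the three kinds of pathway sampled in Aim 3, the one chosen by terminal outcome is chosen for negative terminal states.

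**The concern.** Remission is the only state described as an improvement in the disease, yet none of the named comparisons of care states, pathways or subgroups lists it as the outcome. Because every episode must finish in one of the four terminal states, a patient who recovers and stops attending is recorded as having ceased care, in the same category as a patient who dropped out.

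Table 3 says the analysis of care states against terminal states will help prioritise types of SUD care and decide where services are best delivered. If RMST to ceasing is read without remission beside it, a care type that patients leave because they improved can be flagged as having a retention problem. The Limitations section does not mention this.

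**Working it through.** The plan states no figure on this point, so there is none to reproduce. The check has three parts.

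**1. Where remission enters the plan**

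| Analysis | Quantity named | Remission named as the outcome? |
|---|---|---|
| Contribution of care states (Aim 2, Table 5, Figure 4) | RMST to each terminal state | No |
| Common sequences (Aim 2) | Probability of a sequence ending in a terminal state | No |
| Subgroup comparison (Aim 2) | Occurrence of terminal states | No |
| Guideline-concordant care (Aim 2) | Initiation, engagement, adequacy of treatment | No; these measure process |
| Occupancy plot (Figure 2) | Probability of being in each state over time | Shown, but not compared by care state or pathway |
| Accessibility outputs (text after Table 4) | Transition and hitting probabilities, first passage time and others, per state | Possibly: the text says each state, Table 3 says each care state |
| Models by patient characteristics (end of Aim 2) | Each transition intensity | Possibly, by patient characteristic |

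**2. Can RMST to ceasing mislead?**

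Assume three states: care, remission (R) and ceased (X). All daily rates below are assumptions. Let a be care→R, b care→X, c R→X, and L = a + b. Table 4 counts time in any transient state as event-free, so time in remission counts. For horizon T:

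- RMST = u + [a/(c − L)] × (u − v), where u = (1 − e^(−LT))/L and v = (1 − e^(−cT))/c
- Probability of reaching remission by T, with ceasing as a competing exit = (a/L)(1 − e^(−LT))

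At T = 90 days:

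- Type A, recover and soon leave (a = 0.02, b = 0.002, c = 0.05): u = 39.179, v = 19.778; RMST = 39.179 + 0.7143 × 19.401 = 53.0.
- Type A′, the same but remission lasts longer (c = 0.005): v = 72.474; RMST = 39.179 + 1.1765 × 33.295 = 78.4 (78.35 before rounding).
- Type B, retain with little recovery (a = 0.001, b = 0.006, c = 0.005): u = 66.773, v = 72.474; RMST = 66.773 + 0.5 × 5.701 = 69.6.

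At the three horizons of Table 5:

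| Care type | RMST, 30 d | RMST, 60 d | RMST, 90 d | Remission by day 90 |
|---|---|---|---|---|
| A | 26.55 | 43.53 | 53.04 | 78% |
| A′ | 28.90 | 55.11 | 78.35 | 78% |
| B | 27.46 | 50.41 | 69.62 | 7% |

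A ranks below B at every horizon and A′ above it, although A and A′ have the same probability of reaching remission. RMST to ceasing does not show which type leads to more recovery.

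**3. Does the dating of ceased care matter?**

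Yes. Entry to a care state is itself a service. If ceasing is dated only when the gap has passed 194 days, nobody can reach it within 90 days of entering a care state. RMST to ceasing is then 30, 60 and 90 days for every care type. The hypothetical in Figure 2, where ceasing rises through day 15, suggests dating from near the last visit, but the text does not settle it.

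The pooling of leavers does not depend on dating. Suppose a patient reaches remission and has the last qualifying service on day 150. The gap exceeds 194 days just after day 150 + 194 = 344, which is before day 365. In a one-year comparison this patient counts as ceased under either convention, with nothing to distinguish them from a dropout.

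**The case against.** A reader might infer that pathways are compared on terminal states alone and that remission is never compared. The document does not support that. Study Outcomes names guideline-concordant care as a second type, and both it and the Abstract use open wording (such as, including). Remission is one of the 17 transient states, movement from care states to remission is allowed, and a model is fitted for each transition. The outputs promised after Table 4, and their recalculation by patient characteristics, can be read to include the probability of and time to remission. Self-reported symptoms are used, because they help to build the remission state. Further operational detail sits in appendices that are not shown.

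A reader might also infer that a care type whose patients recover must rank lower. That is not supported either: time in remission counts as event-free, and the order depends on how long remission lasts and how ceasing is dated. The sentence on lower RMSTs is introduced as an example, and in itself says only that such care types more often end in ceasing. The study calls itself exploratory and disclaims causal interpretation.

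All of this stands, and it limits the point. It does not remove it. The per-state outputs are presented as measures of accessibility, Table 3 words that question in terms of care states, and no section specifies remission as an outcome by care state or pathway. The definition of ceased care has no remission condition, and the text around Table 5 goes on from low RMST to action on retention.

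**Conclusion.** The point holds in a limited form. The named outcome comparisons of care states, pathways and subgroups rest on terminal states, none of them favourable, and the other stated outcome type measures process. Remission is in the model but is not specified as an outcome by care state or pathway. Ceased care mixes patients who left in remission with those who disengaged, so RMST to ceasing cannot be read as a retention measure by itself.

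The size cannot be fixed from the document, which gives no remission or ceasing rates. Under the assumed rates, the 90-day difference between the high-remission and low-remission care types runs from 53.0 − 69.6 = −16.6 days, through 0 if ceasing is dated after the gap, to 78.4 − 69.6 = +8.8 days. These figures show that the direction is not determined; they do not predict the study's results. For an exploratory study this is a worthwhile, low-cost improvement and not a flaw that invalidates the design.

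**What to change.** 1. Name remission as an outcome in the Abstract's Methods paragraph and in Study Outcomes.
2. For each care state and each common pathway, report the probability of first remission by fixed times and the time to it, with the terminal states as competing exits. Place these beside the Table 5 RMSTs and add them to the subgroup comparison.
3. Report ceased care split by whether the patient had reached remission earlier in the episode.
4. State the date on which ceased care is entered, since the 30-, 60- and 90-day RMSTs depend on it.
5. Do not interpret RMST to ceasing care without items 2 and 3.

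The cost is mainly additional derived quantities from models already planned, plus wording. The downside is that remission is observed only at assessments or through coded diagnoses. Results should therefore be shown by availability of assessment and will be less precise than those for terminal states.

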**Results:**

This study was funded in June 2025 and received institutional review board approval on July 17, 2025. We expect preliminary data collection for quantitative analyses to be complete by May 2026, and final data collection will be complete by November 2027. We expect qualitative data collection completion by November 2029.

**Conclusions:**

This exploratory study will identify and compare the quality and outcomes associated with common pathways that patients take when they obtain treatment for SUD and provide decision-makers with information on how to better organize SUD care delivery.

## Introduction

Unhealthy substance use, including alcohol, cannabis, and prescription or illegal drugs, is a critical problem for the US health care system. Approximately 30% of people in the United States report unhealthy alcohol use [1,2] and 25% report unhealthy drug use [3]. Substance use contributes to disability and societal costs [4-8]. Substance use disorder (SUD) is a pattern of substance use that causes clinically significant impairment or distress [9,10]. High numbers of deaths driven by overdose from synthetic drugs and counterfeit medications [11], as well as chronic medical complications due to long-term use [12], underscore the urgency of this problem.

Well-defined treatment pathways for SUD exist, and include screening and assessment, behavioral counseling, pharmacological interventions, and/or referral to specialty treatment [13-15]. However, patients with SUD experience substantial challenges in receiving recommended care. Health systems struggle with long wait times that hinder patients’ ability to access SUD care. Clinicians cite challenges in facilitating access to appropriate SUD care and may lack knowledge of available care options. Care coordination is critical for managing patients with SUD, given the wide spectrum of SUD care options, and care is often chronic and prolonged, yet research has found that care is poorly coordinated [16]. Collectively, these challenges result in lengthy follow-up, poorer care communication, and lower clinician ratings [17], and are among the reasons why ≈30% of patients drop out of SUD treatment, compromising treatment effectiveness [18,19]. New solutions are needed to increase access, continuity, and quality of SUD care in health systems.

Studies of SUD care improvements require innovative approaches that consider the dynamic, longitudinal nature of treatment required to address SUD, which has been characterized as a chronic health condition [20,21]. The National Academy of Medicine has encouraged the application of systems approaches to improving health care [22]. As an approach for handling multiple events and time-to-event data within patients, multistate approaches conceptualize health care events and outcomes as states and capture the full sequence of a patient’s care and timing of transitions between states during a care episode [23]. From a multistate modeling perspective, care pathways are defined as the longitudinal sequence of SUD visits that begin where patients were identified (eg, primary care or emergency department [ED]), transition between SUD care types (eg, evaluation and assessment, behavioral treatment and counseling, and pharmacotherapy) [24-26] and settings visited (eg, outpatient, intensive outpatient, or inpatient or residential settings) [27,28], and end in terminal events, such as ceasing SUD care or death. These models capture the dynamics of how patients move through the health system and the probabilities or “intensities” of transitions between states. As a result, multistate approaches have the potential to generate meaningful insights that health systems can use to better organize care delivery for SUD.

This paper presents the protocol for a retrospective cohort study that will apply a multistate approach to nearly 10 years of data from the Kaiser Permanente Washington (KPWA) electronic health record (EHR). This includes health care encounters and patient-reported SUD outcome data from tens of thousands of patients. We will link EHR data to health insurance claims and Washington State death data. This will support a comprehensive exploratory analysis of SUD care transitions that will inform strategies to improve access, continuity, and outcomes in SUD treatment. It also describes our plans to use qualitative research methods to complement the quantitative findings, providing a mixed-methods approach to generate data- and human-driven insights for improving SUD care.

Regarding aim 1, apply multistate models (MSMs) to comprehensively characterize care transitions across the full spectrum of SUD care among patients with alcohol, cannabis, opioid, stimulant, and other SUD. Models will track movement between care states—defined by the SUD care type (eg, pharmacotherapy, behavioral treatment, and counseling) and setting—and characterize the transition probability and time that it takes to move between care states and terminal states.

Regarding aim 2, generate data-driven insights to improve care delivery for SUD using estimated MSMs. We will calculate a broad set of estimates to address critical questions such as the identification of common sequences of care that occur with greater likelihood, the likelihood of guideline-concordant care (eg, adequate doses of services over time), and the likelihood of inefficient care sequences (eg, repeated transitions between inpatient and outpatient states).

Regarding aim 3, observe and explore patient and clinician experiences with care transitions across common care pathways using qualitative research methods. Through interviews and direct observations, we will examine how individuals navigate SUD care, the factors influencing care decisions, and the systemic barriers or facilitators encountered. This aim will be guided by the Chronic Care Model [29] and will integrate insights from both patients and clinicians.

